#### Aim 2c: sustainability

The sustainability plan will be largely descriptive and involve the synthesis of quantitative and qualitative data across implementation outcomes, caregiver satisfaction survey results, and CAB guidance. We will use a mixed-methods data analytic approach (QUANT = QUAL) [94] to develop the sustainability plan.

#### Aim 3

We will apply intent-to-treat analyses, using data from all participants who are randomly assigned to the two arms. Our unbalanced design (200 FCU4Health, 150 services-as-usual) only slightly affects statistical power [95]. The primary outcomes are the distal effects on child weight status and body composition and effects on more proximal mediators, including healthy lifestyle (dietary and physical activity habits), child self-regulation, parenting variables, and use of community support services. The LGC analysis for the continuous BMI and body composition measures will be used to compare the trajectories of the two conditions over time analyzed with random-effects models [96]. Specifically, we will estimate whether individual changes (i.e., growth trajectories) over time vary from person to person and whether inter-individual variation is systematically related to intervention assignment. For comparing FCU4Health and control arms using analysis of covariance (ANCOVA), we have power to detect a mean difference with a small-to-medium effect size (*d* ≥ .25; odds ratio ≥ 1.5, assuming the base rate of the control group is 30%). This means we have power to detect the size of effect on BMI found in previous trials with children and early adolescents, which varies significantly from small to medium (range: *d* = .20–.40) across intervention types [97–100] but is large (*d* ≥ .50) for family-centered behavioral programs [101, 102]. For the growth models (repeated-measures analysis using three or four data points), we have power to detect a small effect on the trajectory (*β* = .12 or *η*^2^ ≤ 2%). LGC modeling has better power than the two-time point ANCOVA for detecting treatment effects in a randomized design [103]. Second, we will examine whether program effects on the distal outcomes are transmitted through the program effects on the proximal variables using mediation analyses, controlling for baseline measures of the mediator and outcome. Bootstrapping will be used to form confidence intervals to test for mediation effects, which has been shown to have better power [86, 104]. We have power to detect a mediated effect if the two paths each have a small-to-medium effect (*β* values ≥ .14).

Baseline weight, ecological risk, minority status, poverty status, and child gender will be included as covariates and tested as potential moderators. Moderation of program effects will be examined by adding a program by moderator interaction in the models of primary outcomes and mediators one at a time. For significant interactions, post hoc probing of simple effects (i.e., effects at different values of the moderator) will be conducted, following Aiken and West [105]. Accounting for the imperfect reliability, we have power to detect moderation effects that account for *R*^2^ ≤ 3% of the outcome [106].

We will examine whether it is necessary to account for site and coordinator effects by calculating the design effect metric [107]. If significant, we will modify our statistical plans and utilize multi-level models with site or coordinator as the cluster variable.

#### Aim 4

To determine differences in family participation between conditions, we will use the Wilcoxon rank-sum tests. We have sufficient power to detect a medium effect for this analysis (*f* ≥ .30). Next, we will use path analysis in structural equation modeling to test a model of program implementation where family engagement mediates the relation between fidelity and clinical outcomes [58]. Using automated fidelity data on the FCU4Health condition sample (*N* = 200), we have power to detect a mediated effect if the two paths each has a small-to-medium effect (*β* values ≥ .21).

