#### Clinical effectiveness of the FCU4Health

Within the two implementation strategy arms, eligible families are randomized to receive either the FCU4Health or clinic services-as-usual plus community program information (see “Methods”). Primary clinical outcomes are child BMI and body composition. Secondary outcomes, hypothesized to mediate effects of the intervention on primary outcomes, are lifestyle behaviors (diet and nutrition, physical and sedentary activity, sleep), child self-regulation, and family management practices.

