## Methods

### Study aims

#### Aim 1

Aim 1 was to finalize the adaptation of the FCU4Health, which was initially adapted and piloted in pediatric primary healthcare [50], based on input from a community advisory board (CAB) and partner clinics.

#### Aim 2

Aims 2 was to evaluate the effects of two delivery strategies: integrated/co-located care and coordinated care with referral. Using a mixed-methods approach applied to Proctor et al.’s [51, 52] taxonomy, we will evaluate the process of implementing the FCU4Health to inform, taking the program to scale.2a. Evaluate fidelity over time to the FCU4Health using a validated observational rating system [53–55] and develop and test an automated fidelity coding system [56].2b. Employ behavioral intervention costing methods [57] to evaluate the costs of installing and delivering the FCU4Health and conduct a cost–benefit analysis to evaluate the monetary benefits of program effects.2c. Develop a plan to support scale-up and sustainment in collaboration with our CAB.

#### Aim 3

Aim 3 was to use pragmatic trial principles to test program effects on primary and secondary outcomes. Intervention effects on proximal outcomes will be tested as mediators on the distal outcomes of child BMI and body composition.

#### Aim 4

Aim 4 was to carefully track utilization in each aspect of the program, gather data concerning family’s service delivery preferences and satisfaction, and test a model of program implementation where family engagement mediates the relation between fidelity and clinical outcomes [58].

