#### Effectiveness

At each assessment, the child and caregiver(s) will be weighed using a portable electronic scale. *BMI* is the primary study outcome because it indicates cardiometabolic disease progression [70–72]. However, improvement in *body composition* in the absence of weight loss can indicate a healthy change in the ratio of fat to lean muscle, which often accompanies significant changes in diet and physical activity and results in metabolic improvement with enduring benefits [73, 74]. At each assessment point, caregivers and children report on *health-promoting family behaviors*; *mealtime, sleep, and media routines*; *child and family physical activity habits*; *child food and beverage choices*; and *use of community support services*. The FITs are used for observational assessment of parenting and family management skills using the validated Coder Impressions Inventory [75] (Dishion T, Hogansen J, Winter C, Jabson J. The coder impressions inventory, unpublished manual). Although not central to our aims, we will also assess several other constructs related to pediatric obesity: *weight-related stigma*, *body image*, *quality of life*, *child behavioral and emotional adjustment*, and *caregiver satisfaction with services*.

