### Data analysis

#### Overview

Analyses focus on implementation data from the families randomized to the FCU4Health. Data from families receiving services as usual will be used in aims 2b and 3. Before data analysis, we will test the psychometric properties (i.e., distribution, reliability) of the measures, conduct a sequence of nested multiple-group confirmatory factor analyses [76] to ensure measurement invariance across language and ethnicity, and apply state-of-the-science data reduction techniques (confirmatory factor analysis, weighted regression scores) by creating multi-indicator, multi-informant construct variables when applicable. These techniques improve measurement properties and result in fewer contrasts, reducing type I error [77]. We expect the attrition rate across waves to be 10–15% based on retention rates for local studies with highly mobile, hard-to-track samples [78, 79]. We will adjust for missing data due to attrition using multiple imputation [80] and full information maximum likelihood [81]. We will perform sensitivity analyses to check the non-response mechanism [82] and attrition analyses to detect differential attrition rates and attrition by group interaction on sociodemographic and pretest variables that may pose a threat to the validity or the equity of the findings [83]. When missingness is not ignorable, we will use complex models to obtain parameter estimates [84]. To estimate power, we used Optimal Design [85] and Monte Carlo simulations in Mplus [84] and referred to relevant publications. All power analyses used 1 − *β* = .80 and *α* = .05 using two-tailed tests. For mediation models, we applied simulation in Mplus for estimating the power of path coefficients and referred to a work by Fritz and MacKinnon [86] for examining significance of mediation effects.

For qualitative data analysis, stakeholder and caregiver interviews and CAB discussions will be audio recorded, transcribed, and then coded using a directed content analysis approach [87] by using existing theory, prior results, and empirical frameworks to develop a coding scheme. Codes will be refined using a subsample of interviews, and then a team of trained coders will code full transcripts. Twenty percent of interviews will be double coded in order to calculate reliability [88]. Disagreements in coding will be resolved via consensus.

#### Aim 1

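### The Aim 3 analysis section lists the proximal mediators as primary outcomes, against the study design section, which makes them secondary; the article also disagrees with itself on whether body composition is primary alongside BMI

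*Protocol article*

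**What the plan says.** The protocol article describes the status of the effectiveness outcomes in five places.

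- Study design, Clinical effectiveness of the FCU4Health: "Primary clinical outcomes are child BMI and body composition". The next sentence reads "Secondary outcomes, hypothesized to mediate effects of the intervention on primary outcomes, are lifestyle behaviors", and goes on to include child self-regulation and family management practices.
- Study aims, Aim 3: the aim is to "use pragmatic trial principles to test program effects on primary and secondary outcomes", with proximal outcomes tested as mediators of the distal ones.
- Measures, Effectiveness: BMI "is the primary study outcome because it indicates cardiometabolic disease progression". Body composition follows as a further indicator of healthy change, with no label.
- Data analysis, Aim 3: "The primary outcomes are the distal effects on child weight status and body composition and effects on more proximal mediators". Four mediator domains are then spelled out in that sentence: lifestyle (diet and activity), the child's self-regulation, parenting, and uptake of community services.
- Data analysis, Aim 3, moderation paragraph: interactions are to be added "in the models of primary outcomes and mediators one at a time".

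On error rates, Data analysis, Overview states "All power analyses used 1 − *β* = .80 and *α* = .05 using two-tailed tests". Its only remark on type I error is that data reduction leaves fewer contrasts.

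**The concern.** The same constructs are secondary in the design section and primary in the analysis section. Use of community support services is less settled still. It is missing from the design section's list of secondary outcomes, Table 1 measures family service participation as an implementation outcome, and Aim 3 makes service use primary.

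The label matters because the two groups of outcomes are different evidence. BMI and body composition are measured on a scale. The mediators rest largely on caregiver and child questionnaires (Table 2), although parenting is also scored from recorded family tasks. The article describes blinding only at baseline, and families then know whether they are receiving the program. Service use is also something the coordinators promote directly through referrals. Under the Aim 3 sentence, a shift in these measures with no change in BMI could be presented as a primary result of a trial whose stated goal is to prevent obesity and excess weight gain.

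The second conflict is smaller but has the same consequence. A reader cannot tell whether an effect on body composition without an effect on BMI is a primary finding.

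**Working it through.** **1. Status of each outcome, by section**

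| Outcome | Study design | Measures, Effectiveness | Data analysis, Aim 3 |
|---|---|---|---|
| BMI / weight status | primary | the primary outcome | primary |
| Body composition | primary | discussed, not labelled primary | primary |
| Lifestyle behaviors | secondary | not labelled | primary |
| Child self-regulation | secondary | not labelled | primary |
| Family management / parenting | secondary | not labelled | primary |
| Use of community support services | not listed | not labelled | primary |

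The count of primary outcomes is therefore 2, 1 and 6. It is 7 if diet and physical activity are counted separately. The statement of Aim 3 and the moderation paragraph both treat primary outcomes as distinct from secondary outcomes or mediators, so the Aim 3 outcome sentence is the outlier on the mediators.

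**2. What the count would mean under one possible success rule**

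The article gives no error rate for the set of outcomes, so there is no figure of its own to reproduce. Assumptions, none of them stated in the article: one test per outcome domain, each at two-sided .05, any one significant result sufficing, and no true effects.

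At least one significant result in either direction, independent outcomes, 1 − .95^k:
- k = 1: 5.0%
- k = 2: 1 − .9025 = 9.8%
- k = 6: 1 − .7351 = 26.5%
- k = 7: 1 − .6983 = 30.2%

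At least one significant result favouring the program, independent outcomes, 1 − .975^k:
- k = 1: 2.5%
- k = 2: 4.9%
- k = 6: 14.1%
- k = 7: 16.2%

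Correlated outcomes (simulation of equally correlated normal test statistics, 400,000 draws, critical value 1.96; the correlations are assumed because the article gives none):

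| Outcomes | Correlation | Either direction | Favourable only |
|---|---|---|---|
| 6 | 0.3 | 24.1% | 12.2% |
| 6 | 0.5 | 20.7% | 10.3% |
| 6 | 0.8 | 13.9% | 7.0% |
| 2 | 0.8 | 7.9% | 3.9% |

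**3. What two primary outcomes would cost in power**

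The article states power for d ≥ .25 by ANCOVA with 200 and 150 families. Without covariate adjustment the detectable difference is (1.960 + 0.842) × √(1/200 + 1/150) = 0.303. It falls to .25 if the baseline–outcome correlation ρ satisfies √(1 − ρ²) = .25/0.303, so ρ ≈ 0.56 with no attrition. The article does not state ρ, so the figure is attainable but cannot be confirmed. If d = .25 is accepted as having 80% power at .05, halving alpha to .025 raises the critical value from 1.960 to 2.241:
- detectable d = .25 × (2.241 + 0.842)/(1.960 + 0.842) = 0.275
- power at d = .25 is Φ(2.802 − 2.241) = Φ(0.560) = 71%

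**The case against.** The best defence is that one sentence is loosely drafted. The design section, the statement of Aim 3 and the moderation paragraph all keep mediators apart from primary outcomes, and Aim 3 itself goes on to speak of distal outcomes and proximal variables. On body composition, the measures section introduces it immediately after BMI with a rationale of its own, which is close to the design section's pairing. This lowers the chance that the authors meant six primary outcomes. It does not remove the conflict, because the sentence stands in the section that governs the effectiveness analysis.

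It can also be said that multiplicity handling is commonly left to an analysis plan, which is not shown here. That is right, and its absence is no part of this point. The contradictory labels are in the current text, and an analysis plan could agree with only one version.

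A reader might go further in two ways that the article does not support. One is to conclude that the trial's .05 error rate is actually broken. The article gives .05 for its power analyses, not as a rule for each outcome test, and never says that success on any one outcome is enough. The two-sided figures also count results in the wrong direction. The other is to conclude that the method for the arm comparison is left open between latent growth curves and ANCOVA. Aim 3 says that the growth curve analysis will be used for BMI and body composition; ANCOVA appears there in the power statement and as a comparator for power.

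Finally, the mediators are not purely self-reported: trained coders score parenting from recorded interactions.

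**Conclusion.** The contradiction is real and needs correcting. Lifestyle, self-regulation and parenting are secondary in one section and primary in another; service use is added as primary in the analysis section only; and body composition is either primary or not, depending on the section. As written, the Aim 3 sentence would permit a mediator-only effect to be labelled a primary result.

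The numerical exposure is conditional. Under an any-one-suffices rule at two-sided .05, six outcomes give 26.5% if independent and 13.9% to 24.1% at correlations of 0.8 to 0.3, against 5% for BMI alone. In the favourable direction the independent figure is 14.1%, against 2.5%. For BMI and body composition alone the inflation is modest: 9.8% if independent and 7.9% at a correlation of 0.8. These figures show why the label needs fixing; they do not estimate the trial's actual error rate.

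**What to change.** Amend the outcome sentence in Data analysis, Aim 3, so that only child weight status (BMI standardised by sex and age, as in Table 2) and body composition are primary. List healthy lifestyle, child self-regulation, parenting variables and use of community support services as secondary or mediator outcomes, in line with the design section, and say that they carry no stand-alone claim of primary effectiveness.

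Then make the design and measures sections agree on body composition, and carry the choice into Aim 3. There are two coherent options:
- BMI is the sole primary outcome and body composition a key secondary outcome. This keeps the full .05 for BMI, but improved body composition without weight loss, which the measures section values, could not be a primary finding.
- Both are primary, with a stated rule for sharing or ordering alpha. An equal split costs power: about 71% at d = .25 in place of 80%, or a detectable d of about 0.275. A fixed order avoids the split, but the second outcome can be claimed only if the first succeeds.

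Correcting the mediator labels is a change of wording and needs no new data, visits or families. The body composition choice is a design decision. Recruitment was already in progress at submission, so both should be dated and recorded before outcomes are compared by arm. The price is that a mediator-only effect can no longer be reported as a primary success.

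### The odds ratio of 1.5 given as detectable in Aim 3 has about 42% power, not 80%, as a binary comparison; the detectable odds ratio is about 1.9

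*Protocol article*

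**What the plan says.** The Overview of the Data analysis section fixes the operating characteristics for every power figure: "All power analyses used 1 − *β* = .80", with two-tailed tests at α = .05. It expects 10–15% attrition across waves.

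Under Aim 3 the allocation is given as "Our unbalanced design (200 FCU4Health, 150 services-as-usual". For the ANCOVA comparison of the two conditions, the article claims power for a mean difference of d ≥ .25. In the same parenthesis it adds an odds ratio of at least 1.5, "assuming the base rate of the control group is 30"%.

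It then draws an inference: "This means we have power to detect the size of effect on BMI found in previous trials with children and early adolescents". It gives the range of those effects as d = .20–.40, and d ≥ .50 for family-centered behavioral programs.

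For the growth models it says "we have power to detect a small effect on the trajectory", given as β = .12 or η² ≤ 2%. The moderation paragraph that follows claims power for effects accounting for R² ≤ 3% of the outcome.

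**The concern.** The odds ratio is printed as a detectable effect, with a control-group rate attached and 80% power as the declared standard. A reader will take it that a binary outcome with 30% in the control group can show an odds ratio of 1.5 with 80% probability. With 350 families that cannot be reproduced. If a dichotomous outcome were later analysed and came out null, the article could be cited as evidence that an odds ratio of 1.5 had been excluded, when the chance of detecting it was below one half.

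The sentence on earlier trials concerns BMI, the primary outcome, and claims slightly more than the article's own floor allows. The two reversed inequalities, read literally, claim power for every effect down to zero.

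**Working it through.** **Inputs.** From the Overview: power .80, two-sided α = .05, attrition 10–15%. From Aim 3: 200 intervention and 150 control, d ≥ .25, odds ratio ≥ 1.5, control rate 30%, earlier effects d = .20–.40.

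**1. The plan's continuous figure.** The unadjusted detectable difference is (1.960 + 0.842) × √(1/200 + 1/150) = 2.8016 × 0.1080 = 0.303. ANCOVA multiplies this by √(1 − r²), where r is the baseline–outcome correlation. Setting 0.303 × √(1 − r²) = .25 gives r ≈ .56. So d ≥ .25 is attainable with a moderate correlation.

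**2. The odds ratio as a binary comparison.**
- Control odds: .30/.70 = 0.4286. Times 1.5 = 0.6429. Intervention rate: 0.6429/1.6429 = .3913. Difference: .0913.
- Pooled rate: (150 × .30 + 200 × .3913)/350 = .3522.
- Standard error under the null: √[.3522 × .6478 × (1/150 + 1/200)] = .0516.
- Standard error under the alternative: √[.30 × .70/150 + .3913 × .6087/200] = .0509.
- Power: Φ[(.0913 − 1.960 × .0516)/.0509] = Φ(−0.193) = 42.4%.

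Other methods agree:

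| Variant | Power |
|---|---|
| Pooled two-proportion test, 200/150 | 42.4% |
| Wald test on the log odds ratio | 42.3% |
| Arcsine | 42.9% |
| Simulation, 40,000 runs | 42.4% |
| One-sided test | 55.0% |
| Odds ratio 1/1.5 (30% vs 22.2%) | 38.0% |
| 10% attrition (180/135) | 38.8% |
| 15% attrition (170/127.5) | 37.0% |

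**3. What is detectable.** Solving the same formula for 80% power gives an odds ratio of 1.88 (30% vs 44.6%) with all 350 families, 1.94 after 10% loss and 1.98 after 15% loss. In the protective direction it is 0.49 with all 350. At the 4:3 allocation, an odds ratio of 1.5 needs about 373 control and 498 intervention families, about 870 in total.

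**4. Where 1.5 probably comes from.** Suppose a normally distributed outcome is cut so that 30% of controls lie beyond the threshold, and the mean is then shifted by d = .25. The intervention rate is Φ(Φ⁻¹(.30) + .25) = Φ(−0.524 + 0.25) = .3919. The odds ratio is (.3919/.6081)/(.30/.70) = 1.504. The logistic conversion, exp(.25 × π/√3) = 1.57, fits less well and needs no base rate. The normal-threshold conversion explains both the 1.5 and the quoted 30%.

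**5. Earlier trials.** If d = .25 has exactly 80% power, its standardised distance is 2.8016. At d = .20 it is .20/.25 × 2.8016 = 2.241, and power is Φ(2.241 − 1.960) = 61%. At d = .40 power is 95.8% and at d = .50 it is 99.6%, even without covariate adjustment.

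**6. Inequalities.** A minimum detectable effect means power of at least 80% at that effect and above. The article writes d, the odds ratio and the mediation paths with ≥, but η² and R² with ≤.

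**The case against.** The strongest defence is step 4: the odds ratio sits in the same parenthesis as d, in a sentence about a mean difference, and is almost exactly d = .25 at a 30% base rate. On that reading it restates one effect on a second scale and no power calculation has failed. As an account of where the number came from, this is convincing. It does not rescue the wording, because the sentence says the trial has power for that odds ratio and nothing marks it as a translation. Dichotomising discards information, so the same underlying shift is harder to detect on the binary scale.

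Covariate adjustment does not close the gap either. The explained variance of about .32 that brings d = .25 to 80% lifts the odds ratio of 1.5 only to about 57%; about 60% would have to be explained.

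It is also fair to say that no binary analysis of weight is specified. The article models BMI and body composition as continuous, and names weight status only in general terms. This limits the consequence of the error.

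On earlier trials, the gap covers only d = .20 up to .25. The cited effects for family-centered programs are much larger, and the article says that growth modelling is more powerful than ANCOVA. The slip is small, but the inference is still drawn from the ANCOVA floor.

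A reader might go further and infer that β = .12 for the trajectory is also wrong. As a single unadjusted coefficient in 350 children it would have about 62% power, but it reaches 80% if other covariates explain about 35% of the variance. The article says simulation was used and does not print the inputs, so the figure is neither reproduced nor refuted.

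**Conclusion.** The claim of 80% power for an odds ratio of 1.5 at a 30% control rate does not hold for a binary outcome: power is about 42% with all families and 37–39% after the expected attrition. The detectable odds ratio is about 1.9, or about 2.0 after 15% attrition. This rests only on stated inputs and a standard unadjusted two-group test. Separately, the article's own ANCOVA floor leaves the low end of the cited BMI range uncovered (about 61% at d = .20, assuming exactly 80% at d = .25), and two inequalities point the wrong way.

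A reader might infer that the whole Aim 3 power statement is wrong or that the trial is underpowered for BMI. The documents do not support that. The d ≥ .25 figure is attainable with a baseline correlation of about .56, and the continuous BMI analysis does not depend on the odds ratio. Nor is it a fault that the article prints neither that correlation nor an attrition allowance beside each figure; such detail can sit in the full protocol or analysis plan.

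**What to change.** Change the wording in Aim 3 and leave the sample size and design alone.

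1. Restate the odds ratio as ≥ 1.9 (about 2.0 after 15% attrition) at a 30% control rate. Alternatively delete it, or label it as d = .25 translated to an odds-ratio scale, with a note that it is not the detectable effect for a binary outcome.
2. Limit the sentence on earlier trials to effects of d ≥ .25, or keep the full range and give the power at d = .20 (about 61%).
3. Turn the inequalities for η² (growth models) and R² (moderation) to ≥, with each threshold confirmed against the power output it came from.

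The cost is a few words. The stated sensitivity for binary outcomes becomes less favourable, and nothing in the conduct or primary analysis of the trial changes.

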**Methods:**

This (type II) hybrid effectiveness–implementation randomized trial tests the Family Check-Up 4 Health (FCU4Health) program, which was designed to target health behavior change in children by improving family management practices and parenting skills, with the goal of preventing obesity and excess weight gain. The FCU4Health is assessment driven to tailor services and increase parent motivation. A sample of 350 families with children aged 6 to 12 years who are identified as overweight or obese (BMI ≥ 85th percentile for age and gender) will be enrolled at three primary care clinics [two Federally Qualified Healthcare Centers (FQHCs) and a children’s hospital]. All clinics serve predominantly Medicaid patients and a large ethnic minority population, including Latinos, African Americans, and American Indians who face disparities in obesity, cardiometabolic risk, and access to care. The FCU4Health will be coordinated with usual care, using two different delivery strategies: an embedded approach for the two FQHCs and a referral model for the hospital-based clinic. To assess program effectiveness (BMI, body composition, child health behaviors, parenting, and utilization of support services) and implementation outcomes (such outcomes as acceptability, adoption, feasibility, appropriateness, fidelity, and cost), we use a multi-method and multi-informant assessment strategy including electronic health record data, behavioral observation, questionnaires, interviews, and cost capture methods.

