### Study participants, recruitment, and randomization

Families with children 5.5 to 12 years of age with BMI ≥ 85th percentile for age and gender at study entry are eligible to participate. Participants will be identified during clinic well- and sick-child visits and through queries of the Electronic Health Record (EHR). Enrolled families will complete an ecological, family health routine assessment. After the first assessment, families will be randomly assigned to the FCU4Health (*n* = 200) or Services-as-Usual Plus Information condition (*n* = 150) using a stratified block randomized design by child gender, age, language (English, Spanish), and ethnicity. Assessing the family prior to randomization ensures double-blinding at baseline. Families in the intervention condition will participate in the FCU4Health program, as outlined in the next section, in addition to receiving usual care through their clinic. Families are compensated for completing assessments, but not for engaging in services. A CONSORT table is presented in Fig. 2.

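### The covariates named for Aim 3 leave out age, language and strategy arm, and take ethnicity only as minority status, although randomisation is balanced on all four

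*Protocol article*

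**What the plan says.** Protocol article, Study participants, recruitment, and randomization: 200 families go to FCU4Health and 150 to services as usual, under a "stratified block randomized design by child gender, age, language (English, Spanish), and ethnicity". Clinical effectiveness of the FCU4Health adds the setting: "Within the two implementation strategy arms, eligible families are randomized to receive either the FCU4Health or clinic services-as-usual plus community program information". One strategy arm is a single hospital clinic and the other is two FQHCs (Implementation strategies and service delivery sites).

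Data analysis, Aim 3, names the adjustment variables: "Baseline weight, ecological risk, minority status, poverty status, and child gender will be included as covariates and tested as potential moderators". The next paragraph deals with site separately: "We will examine whether it is necessary to account for site and coordinator effects by calculating the design effect metric". It continues: "If significant, we will modify our statistical plans and utilize multi-level models with site or coordinator as the cluster variable".

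Table 2 states that child BMI is standardised by sex and age. It states no such standardisation for body composition. Eligible children are 5.5 to 12 years old.

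**The concern.** An analysis should normally carry the factors used to balance the allocation. When the two conditions are balanced on a factor that predicts outcome, the treatment estimate varies less from trial to trial. A model that leaves the factor out does not see this gain. It puts the factor's variance into the residual and reports a standard error that is too large.

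Here the list drops two of the four named stratifiers (age and language) and the strategy arm within which families are randomised. Ethnicity enters only as minority status, which is probably coarser. The agencies describe their families as about 60–65% Latino, 10% African American and 5–8% American Indian, which sums to 75–83%. If minority status is a yes/no variable (an assumption), most families would share one value.

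The article itself gives reasons to expect some prognostic value. The age range is wide, and body composition has no stated age standardisation. Questionnaires are completed in English or Spanish, and the plan tests measurement invariance across language and ethnicity. What is at stake is precision and interval width.

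**Working it through.** **Stratification against covariates**

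| Balanced at randomisation | In the Aim 3 covariate list? |
|---|---|
| Child gender | Yes |
| Age | No |
| Language | No |
| Ethnicity | Only as minority status |
| Strategy arm | No |

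**The plan's own figure.** Aim 3 gives d ≥ 0.25 for the ANCOVA, at 80% power and two-sided α = 0.05 with 200 against 150.

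- Without covariates, detectable d = (1.960 + 0.842) × √(1/150 + 1/200) = 2.802 × 0.1080 = 0.303. Power at d = 0.25 is 63.9%.
- To reach 0.25, covariates must explain R² = 1 − (0.25/0.3026)² = 0.317 of outcome variance, a correlation of about 0.56.
- After the planned 10% or 15% attrition, the required R² is 0.39 or 0.42.

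The article does not state an R², so 0.25 is plausible but cannot be confirmed. It does depend on covariate adjustment.

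**Effect of the omission.** Take R² = 0.317, so that the stated 0.25 has 80% power. The model-based standard error is √0.683 × 0.1080 = 0.0892. Let q be the share of residual variance explained jointly by the omitted factors. The documents do not give q, so it is an assumption shown over a range. With allocation balanced on these factors:

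- true standard error = 0.0892 × √(1 − q)
- type I error = 2Φ(−1.96/√(1 − q))
- power, omitted = Φ[(0.25 − 1.96 × 0.0892)/true standard error]
- power, adjusted = Φ[0.25/true standard error − 1.96]
- detectable d, adjusted = 0.25 × √(1 − q)

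| q | Model SE / true SE | Type I error | Power, omitted | Power, adjusted | Detectable d, adjusted |
|---|---|---|---|---|---|
| 0% | 1.000 | 5.0% | 80.0% | 80.0% | 0.250 |
| 2% | 1.010 | 4.8% | 80.2% | 80.8% | 0.247 |
| 5% | 1.026 | 4.4% | 80.6% | 82.0% | 0.244 |
| 10% | 1.054 | 3.9% | 81.3% | 84.0% | 0.237 |
| 15% | 1.085 | 3.4% | 81.9% | 86.0% | 0.230 |

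The like-for-like loss is the difference between the two power columns: about 0.6, 1.4, 2.7 and 4 points for q = 2%, 5%, 10% and 15%. Comparing the adjusted figure with a flat 80% would overstate it, because balance already reduces the true variance under either model.

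**Simulation check.** There were 4,000 runs per setting, with permuted blocks of 7 at 4:3 within strata of sex, age, language, ethnicity and strategy arm. Block size and stratum prevalences are assumptions. At q = 10%, type I error was 3.7% omitted and 4.8% adjusted, and power was 79.5% and 82.5%. The 3-point gap agrees with the formula.

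**The case against.** The strongest reply has five parts.

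- **The main models are growth curves.** Aim 3 compares BMI and body-composition trajectories with random effects. Stable differences in level by age or language go largely into the random intercept. Omission then affects the slope test mainly to the extent that these factors predict rate of change. This stands. The figures above apply to the single-endpoint ANCOVA and should not be read across to the slopes.
- **BMI is already standardised for age and sex.** This also stands. For BMI, the age part of q may be close to zero.
- **The size rests on an assumption.** True: q must be variance left after the listed covariates, and at q = 0 nothing changes.
- **Site is already planned for.** A reader might infer that site is ignored, or that families are randomised within agency. The documents support neither. Randomisation is stated to be within the two strategy arms, and the Aim 3 text provides a design-effect check with multi-level models as fallback. What remains is that this choice is data-driven, that three sites are too few to estimate a between-site variance, and that the fallback does nothing for age or language.
- **The article condenses a fuller plan.** The covariate sentence does not claim to be exhaustive, and an analysis plan could add terms. That limits the weight of the point. Still, the article names specific covariates that do not match its own stratification, and no other part of it restores the missing ones.

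A reader might also take baseline weight to mean raw weight in place of the baseline outcome. The article does not say so. It uses weight for the outcome domain generally, and the mediation models control for baseline values of mediator and outcome.

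**Conclusion.** The mismatch is real and its effect is modest. If the named covariates are used as written, age, language and strategy arm are left out of the Aim 3 models and ethnicity is probably coarsened. Where these factors are prognostic, standard errors are somewhat too large and tests are conservative.

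For the single-endpoint ANCOVA, an assumed q of 2–10% puts type I error at 4.8–3.9% and costs about 0.6 to 2.7 points of power. The loss is probably less for standardised BMI and for growth-curve slopes. It is probably more for outcomes without stated age standardisation, such as body composition, but the documents do not allow a figure for that.

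A reader might infer that the confidence intervals are invalid or the effect estimates biased. That does not follow: the intervals are at most slightly wide. This is a worthwhile improvement in precision and does not threaten the trial's conclusions.

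**What to change.** State in the Aim 3 analysis that the growth, ANCOVA and mediation models include, as prespecified fixed covariates, child age, language, ethnicity in the categories used for stratification, and strategy arm. The three-level site can replace strategy arm, because it contains it (one hospital clinic in one arm, two FQHCs in the other). Keep gender and the other listed covariates.

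Do not leave site to the design-effect check alone. With three sites, fixed terms are safer than an estimated between-site variance. The check can still be used for coordinator.

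The change is to wording only. The stratifiers and site are already recorded. Age and language take one degree of freedom each (age as a linear term), site takes two, and ethnicity takes one fewer than its number of categories, from 350 families.
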